### Sample collection

2.6

#### Human samples

2.6.1

Clinical samples, such as urine, sputum cultures, percutaneous aspirations, and exudates, will be collected during routine clinical care when clinically indicated through the pre-intervention and intervention phases and analyzed in the laboratory of each participating center. To identify carriers of MDR bacteria (carrier screening samples), nasal swabs will be collected to detect MRSA and rectal or perianal swabs to detect ESBL- and carbapenemase-producing *Enterobacterales*, MDR *P. aeruginosa* and *A. baumannii*, from residents in centers participating in wastewater analysis. These screening samples will be collected quarterly by nurses from residents who have provided written informed consent, during the intervention phase, between the first and the last day of this phase. These samples will be collected using swabs, sent in a bacterial transport medium, and processed in the same way as clinical samples for the phenotypic study in the coordinator center’s laboratory.

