### Intervention

2.2

The intervention consists of the implementation of antimicrobial stewardship strategies through the EduFAST web platform in participating NHs, to optimize antimicrobial use, improve infection management, and strengthen surveillance of antimicrobial resistance.

The intervention phase began at the end of 2025 and will continue throughout 2026. During this period, healthcare professionals from participating NHs will have access to the EduFAST platform and will be encouraged to use its different modules as part of routine clinical practice.

The intervention includes three main components:Educational component. Healthcare professionals will have access to training materials hosted on the platform, including treatment guidelines for the most common infectious syndromes in NHs, audiovisual materials, infographics, and simulated clinical cases. Participants will complete questionnaires assessing baseline knowledge, acquired knowledge, and satisfaction with the training activities.Monitoring of antimicrobial use and resistance indicators. Participating centers will enter monthly data on antimicrobial consumption, clinical outcomes, and microbiological indicators. The platform will automatically calculate predefined indicators, allowing centers to monitor antimicrobial use and resistance trends.Results reporting and feedback. The platform will generate periodic reports summarizing the indicators for each participating center. These reports will allow users to compare their center’s results with aggregated data from other participating NHs and will provide recommendations to improve antimicrobial prescribing practices and infection management.

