#### Sample size

2.3.2

The sample size has been calculated based on the results of the multicenter study ‘PROA-SENIOR’ (13). Considering an intraclass correlation coefficient of 0.21, a coefficient of variation between center for total antimicrobial consumption (the main variable) of 0.41, and an average of 110 residents per center, with an alpha risk of 5%, a power of 80%, and a detection of the effect size of 20%, the required sample size is 9 centers. Adding a 10% loss, the minimum sample size obtained is 10 NHs. For the wastewater analysis, three participating NHs will be selected.

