#### Wastewater samples

2.6.2

For the analysis of wastewater in the selected NHs, a sample of between 500 and 1,000 mL will be collected from the drainage manhole of each center once a month between 8:00 and 10:00 a.m. A total of at least 24 samples will be collected throughout the study (12 during the pre-intervention phase and 12 during the intervention phase). If a center has more than one drainage manhole, samples will be collected from all of them. These samples will be transported under refrigeration to the coordinating center. There, four 50 mL aliquots will be prepared: two will be used to determine the levels of antimicrobials and their metabolites, and the other two for the analysis of microorganisms and resistance genes.

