### Statistical analysis

2.9

A descriptive analysis will be performed. Continuous variables will be expressed as measures of central tendency and dispersion, such as mean ± standard deviation or median and interquartile range, depending on the distribution. Categorical variables will be expressed as absolute and relative frequencies.

Interrupted Time Series Analysis (ITSA) will quantify changes in the level (immediate effect) and trend (sustained effect) of outcomes associated with implementing the web platform, considering the study’s longitudinal and ecological nature. ITSA will be performed using a segmented regression model to estimate four parameters: baseline level, baseline trend, the change in level immediately following the intervention, and the change in trend following the intervention. Seasonal adjustment will be applied to those time series in which seasonality were detected. The model incorporates an autoregressive term to account for the autocorrelation present in the time series data. To assess variability and the overall effect across different centers, we will use a linear mixed model (LMM) for repeated measures that includes a random intercept for center. Potential confounders will be managed as fixed effects covariates. *Post hoc* comparisons of estimated marginal means will be performed with the Bonferroni correction applied to adjust for multiple comparisons.

We will evaluate the correlations between the presence of MDR microorganisms and their resistance profiles in wastewater, clinical, and carrier screening samples. We will also evaluate the correlations between antimicrobial concentrations in wastewater and consumption data from centers. We will assess the strength and direction of these correlations using the appropriate Pearson or Spearman correlation coefficient. Then, we will perform univariate and multivariable linear regression analyses to further explore the relationships.

All statistical analyses will be performed using two-tailed tests in IBM SPSS Statistics and R statistical software. A *p*-value of less than 0.05 will be considered statistically significant.

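### Carrier screening runs only in the intervention phase and only in the three wastewater homes; if its results reach those homes, their before/after change reflects platform plus screening

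*Protocol article*

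**What the plan says.** **The intervention.** Section 2.2 of the protocol article states that "The intervention includes three main components" and lists education, indicator monitoring, and reporting with feedback. Carrier screening is not listed.

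**The screening.** Section 2.6.1 adds nasal and rectal or perianal swabs for MDR carriage, taken "from residents in centers participating in wastewater analysis". On timing it states: "These screening samples will be collected quarterly by nurses from residents who have provided written informed consent, during the intervention phase". The window given is "during the intervention phase, between the first and the last day of this phase". Routine clinical samples, by contrast, run through both phases. The swabs are processed at the coordinating center's laboratory.

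**The homes.** Section 2.3.2: "For the wastewater analysis, three participating NHs will be selected". Wastewater is sampled in both phases, "12 during the pre-intervention phase and 12 during the intervention phase" (section 2.6.2).

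**The analysis.** Section 2.9 plans segmented regression with level and trend changes, which it ties to implementing the platform. It adds a "linear mixed model (LMM) for repeated measures that includes a random intercept for center", with unspecified confounders as fixed-effect covariates. For wastewater it plans correlations and regressions. The abstract and the discussion (section 3) also say the wastewater data will serve to judge the intervention's environmental impact.

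The limitations paragraph names the before-after design and differences between homes. It does not mention the added screening.

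**The concern.** In the three wastewater homes, something other than the platform also changes between the phases: residents are actively screened for MDR carriage. Knowledge of carriage could alter infection control or prescribing, and through these consumption, resistance and effluent. A before/after design credits whatever changes at the phase boundary to the declared intervention.

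The random intercept for center does not protect against this. It absorbs differences between homes that are constant over time, not a change that arrives with the phase. Two readings are exposed:

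- the pooled consumption effect, in part, because three of the homes carry the extra activity;
- any before/after statement about effluent, in full, because every home that supplies wastewater is screened.

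**Working it through.** **The plan's own figure.** Section 2.3.2 gives 9 centers, and 10 after 10% loss. The loss step reproduces: 9 / (1 − 0.10) = 10. The formula behind the 9 is not named. One form that comes close is a one-sample comparison with 12 monthly repeats: 7.849 × 0.41² / 0.20² × (1 + 11 × 0.21) / 12 = 32.98 × 0.276 = 9.1. Other plausible forms give quite different numbers, so the 9 is neither confirmed nor shown wrong. The point does not depend on it; below it is taken as given.

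**Step 1: overlap of screening and phase.**

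| Homes | Before | Intervention phase |
|---|---|---|
| 3 wastewater homes | no platform, no screening | platform and screening |
| Other homes (7 of 10) | no platform, no screening | platform only |

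In the wastewater homes the screening indicator equals the phase indicator. With outcome = a + b·phase + c·screening, only b + c can be estimated from them. Across all ten homes c is estimable in principle, because seven homes are unscreened.

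**Step 2: dilution in the pooled consumption estimate.** Assume equal weights, a platform effect p and a screening effect s acting multiplicatively. No value of s is in the documents, so a range is shown.

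- Screened homes: (1 + p)(1 + s) − 1
- Pooled, 10 homes: [3 × screened-home change + 7 × p] / 10

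| p | s | Screened homes | Pooled |
|---|---|---|---|
| 0 | −20% | −20% | −6.0% |
| 0 | −10% | −10% | −3.0% |
| 0 | +10% | +10% | +3.0% |
| −20% | −20% | −36% | −24.8% |
| −20% | −10% | −28% | −22.4% |
| −20% | −5% | −24% | −21.2% |
| −20% | +5% | −16% | −18.8% |
| −20% | +10% | −12% | −17.6% |

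The pooled estimate moves by 3/10 of the shift in the screened homes (3/9 if only nine homes remain). For screening alone to produce a pooled fall of 20%, consumption in the three homes would have to fall by 0.20 / 0.3 = 67%.

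**Step 3: dilution in the wastewater contrast.** The share is 3/3, so the whole of any screening effect is carried.

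**Step 4: what the analysis can recover.** Take 80% power for 20% at nine homes as given, two-sided 5%, so that 20% equals 2.802 standard errors at nine homes.

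- *Seven unscreened homes:* power = Φ(2.802 × √(7/9) − 1.96) = Φ(0.51), about 70%. The effect detectable with 80% power is 20% × √(9/7) = 22.7%.
- *Screening-home by phase term, 3 against 7 homes:* detectable difference = 20% × 3 × √(1/3 + 1/7) = 41%. A screening effect of the sizes in the table would almost always be missed.

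**The case against.** The strongest reply is that the mechanism is not in the text. No section says that carrier results reach the homes or change care. The swabs go to the coordinating laboratory, their stated use is the correlation with wastewater and clinical isolates, and an article may leave the return of results to the full protocol. This stands, and it is why the point is conditional. The condition is not far-fetched, however. Section 2.5 lists swab isolates among the monthly variables and says intervention-phase data are collected using the platform; section 2.4 lets participants view their own indicators and download recommendations. That is a possible route for aggregate counts, though not evidence that individual carrier status is returned.

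Four stronger readings are tempting and are not supported:

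- *That screening starts on the first day of the phase.* Section 2.6.1 gives a window with quarterly rounds. Any response to results would follow the first round. This does not create an unscreened wastewater home.
- *That the model has only a single phase effect and cannot handle screening at all.* Section 2.9 plans level and trend changes and allows covariates. For consumption, a screening term could be fitted; the difficulty is its low power.
- *That the trial loses a stated amount of power.* The screening effect is unknown in size and sign, and the article does not give the standard error of the pooled estimate, so no such figure can be claimed.
- *That the planned wastewater analysis is invalid.* Section 2.9 plans correlations and regressions there. The problem attaches only to a before/after claim of environmental impact, which the abstract and discussion make.

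The before-after design is already named as the main limitation. That general caveat covers unknown concurrent changes; this one is known and introduced by the study itself.

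**Conclusion.** The point holds in conditional form. Screening is confined to the intervention phase and to the three wastewater homes, and it is not part of the declared intervention. If swab results reach those homes, which the article does not state, their before/after change is the joint result of platform and screening.

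For consumption the consequence is modest: about 30% of any screening effect enters the pooled estimate, assuming ten equally weighted homes, with size and direction unknown. For wastewater the confounding is complete, and no model fitted to these three homes can remove it. If results were withheld from the homes, little of the concern remains.

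**What to change.** 1. Record, for each of the three homes, whether and when swab results were made available, individually or as counts on the platform. This is easier to log now, with the intervention phase under way, than to reconstruct later.
2. Keep the all-home analysis as the main one. Prespecify a sensitivity analysis of consumption and clinical indicators that excludes the three screened homes.
3. Unless results were withheld, describe any before/after change in effluent as occurring under platform plus carrier screening, wherever environmental impact is discussed.
4. A screening-home by phase term may be reported as exploratory. A null result should not be read as reassurance, since 80% power is reached only for a difference of about 41%.

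This needs no new samples: one extra model run, a short log and changed wording. The downside is precision. Seven homes is below the nine that section 2.3.2 requires, so the sensitivity estimate supports or questions the main result but cannot replace it.

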#### Wastewater samples

2.6.2

For the analysis of wastewater in the selected NHs, a sample of between 500 and 1,000 mL will be collected from the drainage manhole of each center once a month between 8:00 and 10:00 a.m. A total of at least 24 samples will be collected throughout the study (12 during the pre-intervention phase and 12 during the intervention phase). If a center has more than one drainage manhole, samples will be collected from all of them. These samples will be transported under refrigeration to the coordinating center. There, four 50 mL aliquots will be prepared: two will be used to determine the levels of antimicrobials and their metabolites, and the other two for the analysis of microorganisms and resistance genes.

### Microbiological analysis

2.7

#### Human samples

2.7.1

For phenotypic characterization, selective culture media will be used for the recovery of MDR microorganisms (Thermo Scientific™ Brilliance™ ESBL/Brilliance CRE biplate). The media will be incubated for 48 h, with a first reading at 24 h, under aerobic conditions at 35–37 °C. The MicroScan Walkaway semi-automated microdilution system (Beckman Coulter Inc., USA) will be used for the identification and susceptibility study. The analysis of antibiotic susceptibility and resistance mechanisms will be performed according to the criteria of the European Committee on Antimicrobial Susceptibility Testing (EUCAST) (28).

The following criteria will be applied to the MDR classification described in Table 3.

**Table 3 tab3:** Definitions of MDR classification.

Multidrug-resistant organisms	Definitions
Carbapenemase isolate	If the isolate produce both ESBL and carbapenemase
ESBL-producing isolate	If the isolate is resistant to meropenem, imipenem, and/or ertapenem but does not produce carbapenemases and produces ESBL
MDR *P. aeruginosa*	If the isolate is resistant to carbapenems or ≥3 classes of antipseudomonal agents (penicillins [piperacillin-tazobactam], cephalosporins, carbapenems, quinolones, or aminoglycosides)
MDR *A. baumannii*	If the isolate is resistant to carbapenems or ≥3 classes of antibiotics (penicillins [piperacillin-tazobactam], cephalosporins, carbapenems, quinolones, or aminoglycosides)

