To evaluate the impact of the web platform as an ASP tool and assess the potential of using wastewater for surveillance, the following variables will be recorded monthly:*Variables related to the use of the web platform*: number of visits to the web platform, number of NHs registered, activity on the web platform (reports, completed training, etc.), and the average score on knowledge and satisfaction questionnaires.*Variables of antimicrobial use*: Defined Daily Dose (DDD) according to the World Health Organization (27), globally (Anatomical Therapeutic Chemical (ATC) groups J01 + J02), and for specific antimicrobials (amoxicillin, amoxicillin/clavulanic acid, cefixime, other cephalosporins, azithromycin, clarithromycin, ciprofloxacin, levofloxacin, moxifloxacin, clindamycin, metronidazole, sulfamethoxazole/trimethoprim, and fosfomycin trometamol). We will also record the number of prescriptions for the aforementioned antimicrobials, both individually and globally.*Clinical variables*: number of residents, number of hospital admissions, number of hospital admissions due to infections, and number of hospital admissions due to adverse effects of antimicrobials.*Microbiological variables*: number of isolations of MDR microorganisms (ESBL-producing *E. coli*, ESBL-producing *Klebsiella pneumoniae*, carbapenemase-producing *Enterobacteriaceae*, MRSA, MDR *P. aeruginosa*, and MDR *A. baumannii*) in clinical samples and also in nasal and rectal or perineal swab samples (only in selected NHs); and number of DNA or toxin detection for *C. difficile* in clinical samples.*Environmental variables (only in selected NHs)*: concentration of antimicrobials and their metabolites (amoxicillin, methylated amoxicillin, (5R,5S)-amoxicillin, clavulanic acid, cefixime, azithromycin, clarithromycin, levofloxacin, ciprofloxacin, moxifloxacin, clindamycin, clindamycin sulfoxide, metronidazole, hydroxy-metronidazole, sulfamethoxazole and trimethoprim), and concentration of MDR microorganisms (ESBL-producing *E. coli*, ESBL-producing *K. pneumoniae*, carbapenemase-producing *Enterobacteriaceae*, MRSA, MDR *P. aeruginosa*, MDR *A. baumannii*) in wastewater samples.

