#### Wastewater samples

2.7.2

Active surveillance will be carried out for the presence of MDR microorganisms in the wastewater from selected NHs. Simultaneously, phenotypic and molecular characterization will be performed.

From each wastewater sample, 50 mL aliquots will be obtained and centrifuged at 12,000 rpm for 10 min. From the bacterial pellet obtained, an amount equivalent to 5 μL will be taken and resuspended in 500 μL of nucleic acid-free water. Then, 10 μL will be taken and quantitatively plated on Columbia blood agar. For the detection of MDR bacteria, 10 μL will be taken and planted in selective media. Then, the same process described for clinical samples will be performed for phenotypic characterization. For molecular characterization, the MDR Direct Flow Chip® system (Vitro S.A., Granada, Spain) (29) will be used, based on a polymerase chain reaction (PCR) and reverse hybridization system that allows the detection of five bacterial species (*S. aureus, P. aeruginosa, E. coli, K. pneumoniae* and *A. baumannii*), as well as 56 genetic determinants of antibiotic resistance.

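### No stated culture method fits the nasal swabs taken to find MRSA, and no stated route clearly yields the wastewater MRSA concentration

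*Protocol article*

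**What the plan says.** **Targets.** Section 2.6.1 gives the nasal swab one purpose: "nasal swabs will be collected to detect MRSA". Rectal or perianal swabs cover the Gram-negative organisms. Section 2.5 makes MRSA one of six organisms whose isolations are counted "in clinical samples and also in nasal and rectal or perineal swab samples (only in selected NHs"). It also lists MRSA among the organisms in the wastewater variable, "and concentration of MDR microorganisms (ESBL-producing" and so on, which is a concentration and not only presence.

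**Method for swabs.** Section 2.6.1 sends them to the coordinating laboratory, to be "processed in the same way as clinical samples for the phenotypic study". Section 2.7.1 describes that study: "selective culture media will be used for the recovery of MDR microorganisms (Thermo Scientific™ Brilliance™ ESBL/Brilliance CRE biplate"), then fixed incubation conditions, a named semi-automated system for identification and susceptibility, and EUCAST criteria. Table 3 defines carbapenemase and ESBL isolates, MDR *P. aeruginosa* and MDR *A. baumannii*. It has no entry for MRSA.

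**Method for wastewater.** In section 2.7.2 the suspension is "quantitatively plated on Columbia blood agar". A separate portion goes onto selective media, with no product named, after which "the same process described for clinical samples will be performed for phenotypic characterization". A PCR and reverse-hybridization chip is added. It detects five species, *S. aureus* among them, and 56 resistance determinants.

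**Use.** Section 2.9 correlates MDR organisms and resistance profiles across wastewater, clinical and carrier screening samples.

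**The concern.** A swab collected only for MRSA is routed to a plate whose two halves are named for ESBL and carbapenem resistance. Elsewhere the article ties ESBL production to enterobacteria, *E. coli* and *K. pneumoniae*. MRSA is Gram-positive and resistant by a different mechanism. The identification system acts on what has grown, so it cannot report an organism that the plate did not recover.

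At stake is the validity of a negative result. If swabs handled this way are recorded as MRSA-negative, the article would report low or absent carriage as a finding. Clinical MRSA isolates come from each center's own laboratory and would still appear. The comparison could then show discordance between clinical and screening samples that comes only from the method. Swabbing is quarterly and confined to the intervention phase, which the article describes as under way, so a round lost to an unsuitable plate may not be recoverable.

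**Working it through.** The article states no figure to reproduce here. The check sets the sections side by side and then uses one identity to show the size.

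**Step 1. Target against stated method**

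| Source | MRSA variable (2.5, 2.6.1) | Stated culture route | Stated molecular route |
|---|---|---|---|
| Nasal swabs | Number of isolations | ESBL/CRE biplate (2.7.1) | None |
| Wastewater | Concentration | Blood agar, quantitative; selective media, product not named; then the 2.7.1 process | Chip: *S. aureus* and 56 determinants |
| Routine clinical samples | Number of isolates | Each center's own laboratory (2.6.1) | Not applicable |

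Only the first row has no stated route that fits its target. The second has a route to presence but no clear route to a concentration. The third is not shown to be affected.

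**Step 2. Effect on swab carriage**

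Observed carriage = true carriage × sensitivity (specificity taken as 1). Carriage and sensitivity are both assumptions, since the documents give neither.

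| True carriage | Sensitivity 0 | Sensitivity 0.5 |
|---|---|---|
| 5% | 0% | 2.5% |
| 10% | 0% | 5% |
| 20% | 0% | 10% |

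A correlation coefficient divides by the standard deviation of each series. With sensitivity 0 the swab series is constant, its standard deviation is 0 and the coefficient is undefined. The series is short in any case: 3 homes × 4 quarterly rounds in 12 months = 12 home-quarters.

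**Step 3. Illustrative counts**

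Assume 50 consenting residents per home: 3 × 50 × 4 = 600 swabs. Positives at 5%, 10% and 20% are 600 × 0.05 = 30, 600 × 0.10 = 60 and 600 × 0.20 = 120. At sensitivity 0 all are missed. At 0.5, half are missed: 15, 30 and 60. The counts scale in proportion to the number consenting, which the article does not give.

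**Step 4. Wastewater presence**

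For two independent routes, combined sensitivity = 1 − (1 − culture)(1 − chip). With culture at 0 and the chip at an assumed 0.5 to 0.9, this gives 1 − 1 × 0.5 = 0.5 up to 1 − 1 × 0.1 = 0.9. Presence of *S. aureus* therefore need not read as zero.

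**Step 5. Wastewater concentration**

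The chip is described as a detection method, so the text offers no count from it. It reports species and resistance determinants, and the article does not say how a determinant found in a mixed sample would be assigned to *S. aureus*. Blood agar is plated quantitatively, but section 2.7.2 gives the search for MDR bacteria to the separate selective step, which then follows 2.7.1. No stated route clearly ends in an MRSA concentration.

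**The case against.** **The article is condensed, and its bracketed product need not be the only plate.** The text does not say that no other medium is used, and a list of plates by specimen type could sit in a laboratory manual. This stands in part: a zero reading is conditional on there being no unlisted medium. It does not remove the mismatch. The article does not defer the medium elsewhere; it fixes brand, incubation and analyser, and the product it fixes does not fit one of the targets it names.

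**Section 2.7.1 covers human samples, and clinical samples are cultured elsewhere too.** That shows the section does not list every medium used in the study. But the swabs go to the coordinating laboratory, and 2.7.1 is the only phenotypic process described for them.

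**Plate selectivity is not in the documents.** Correct. The inference rests on the plate's name and basic microbiology, so a sensitivity of 0 is an assumption and not a sourced figure.

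**The missing Table 3 row shows little, because MRSA is defined by its name.** Largely fair. Alone it would be minor; it matters because the table and the named medium omit the same organism.

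**A reader might infer that wastewater MRSA must also read as zero.** The documents do not support this. Blood agar is also named, and the chip detects *S. aureus*. The aims and section 2.9 speak of presence and resistance profiles, which the chip informs. Only the concentration lacks a clear route.

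**Conclusion.** The point holds for nasal swabs: as written, the plan names no means suited to recovering the organism for which the swab is taken. If no other medium is used, MRSA carriage is under-detected or reads as zero, and its correlation with the other two sources is uninformative or undefined. For wastewater the point is limited to the MRSA concentration listed in section 2.5.

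Severity is moderate. It touches one of six organisms, in a secondary correlation analysis, in three homes. The main variable is total antimicrobial consumption, and the swabs are taken only in the intervention phase, so they do not enter the before-after comparison.

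A reader might go further and conclude that MRSA results are invalid throughout the study. That is not supported: the monthly clinical MRSA indicator comes from local laboratories and is not shown to be affected. The 30, 60 and 120 missed swabs likewise illustrate scale under assumed numbers and are not estimates for this study.

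**What to change.** - **Section 2.7.1:** plate nasal swabs on an MRSA-selective medium, with *S. aureus* identification and methicillin-resistance testing under the EUCAST criteria already cited. Keep the ESBL/CRE biplate for rectal or perianal swabs.
- **Table 3:** add an MRSA row.
- **Section 2.7.2:** add an MRSA-selective plate for the wastewater count, or restrict the wastewater MRSA variable in section 2.5 to chip-based presence of *S. aureus* and resistance determinants.
- **Data and analysis:** code MRSA as 'not tested', not 'not detected', for any sample already processed without a suitable medium, and leave those samples out of the MRSA correlations.

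The cost is one plate swap per nasal swab and at most one extra plate per wastewater sample, with no added procedure for residents. If a suitable medium is already in use, a sentence naming it in 2.7.1 settles the swab part, and one in 2.7.2 saying how MRSA is counted settles the wastewater part.

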
**Table 2 tab2:** Indicators from the EduFAST study.

Indicator		Definition
Antimicrobial use indicators	Numerators	Monthly total Defined Daily Dose (DDD) of antimicrobials (ATC groups J01 + J02) Monthly DDD of specific antimicrobials (amoxicillin, amoxicillin/clavulanic acid, cefixime, other cephalosporins, azithromycin, clarithromycin, ciprofloxacin, levofloxacin, moxifloxacin, clindamycin, metronidazole, sulfamethoxazole/trimethoprim, fosfomycin trometamol, and other antimicrobials) Monthly number of total antimicrobial prescriptions (ATC groups J01 + J02) Monthly number of prescriptions of specific antimicrobials
	Denominator	Number of residents in the month
Clinical indicators	Numerators	Monthly number of hospital admissions Monthly number of hospital admissions due to infections Monthly number of hospital admissions due to adverse effects of antimicrobials
	Denominator	Number of residents in the month
Microbiological indicators	Numerators	Monthly number of extended-spectrum beta-lactamase-producing *Escherichia coli* isolates Monthly number of extended-spectrum beta-lactamase-producing *Klebsiella pneumoniae* isolates Monthly number of carbapenemase-producing *Enterobacteriaceae* isolates Monthly number of methicillin-resistant *Staphylococcus aureus* isolates Monthly number of multidrug-resistant *Pseudomonas aeruginosa* isolates Monthly number of multidrug-resistant *Acinetobacter baumannii* isolates Monthly detection of DNA or toxin for *Clostridioides difficile*
	Denominator	Number of residents in the month

The flowchart corresponding to the web platform menu, which can only be accessed by participating users is shown in Figure 2.

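### Read literally, Table 3 gives no class to carbapenem-susceptible ESBL producers or to carbapenemase-only isolates, which conflicts with the Table 2 indicators

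*Protocol article*

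**What the plan says.** Section 2.7.1 introduces the table with "The following criteria will be applied to the MDR classification described in Table 3", and the table is titled "Definitions of MDR classification". Two of its four rows concern ESBL and carbapenemase:

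- The row for ESBL producers applies "If the isolate is resistant to meropenem, imipenem, and/or ertapenem but does not produce carbapenemases and produces ESBL".
- The row for carbapenemase producers has a different condition, namely "If the isolate produce both ESBL and carbapenemase".

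The other two rows cover MDR *P. aeruginosa* and MDR *A. baumannii*.

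Table 2 (section 2.4) sets the counted indicators, among them "Monthly number of extended-spectrum beta-lactamase-producing *Escherichia coli* isolates", the same count for *K. pneumoniae*, and "Monthly number of carbapenemase-producing *Enterobacteriaceae* isolates". None carries a condition on carbapenem resistance or on co-production of a second enzyme. The variable list in section 2.5 uses the same unrestricted names, and so does the description of the rectal or perianal screening swabs in section 2.6.1. For wastewater isolates, section 2.7.2 states that "the same process described for clinical samples will be performed for phenotypic characterization".

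**The concern.** A classification table should place every isolate that the indicators are meant to count. These two rows do not. One makes carbapenem resistance a condition for being called an ESBL producer, and the other makes ESBL production a condition for being called a carbapenemase isolate. Table 2 imposes neither condition.

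Two things are at stake. The first is undercounting of the ESBL and carbapenemase indicators if the table is followed. The second is comparability. Clinical samples are analysed in each participating center's laboratory, and screening swabs in the coordinating center's laboratory (section 2.6.1). Pre-intervention data went into a spreadsheet form, and intervention data go into the platform (section 2.5). If some laboratories follow Table 3 and others the plain Table 2 names, two things can go wrong:

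- The correlations in section 2.9 between wastewater, clinical and carrier isolates would compare different classes.
- If the rule changed between phases, the segmented regression could show a level change in an ESBL or carbapenemase indicator that comes from the definition alone.

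**Working it through.** The documents give no figure for this point, so there is none to reproduce. The check is a logical enumeration.

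**Inputs.** The two Table 3 rules as printed (section 2.7.1) and the Table 2 indicator names (section 2.4).

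- Rule A, carbapenemase isolate: ESBL = yes and carbapenemase = yes.
- Rule B, ESBL-producing isolate: ESBL = yes, carbapenemase = no, carbapenem-resistant = yes.

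**Step 1. Apply both rules to every combination.** Three yes/no features give 2 × 2 × 2 = 8 combinations.

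| ESBL | Carbapenemase | Carbapenem-resistant | Table 3 class | Table 2 name that fits |
|---|---|---|---|---|
| yes | yes | yes | carbapenemase | ESBL and carbapenemase |
| yes | yes | no | carbapenemase | ESBL and carbapenemase |
| yes | no | yes | ESBL | ESBL |
| yes | no | no | **none** | ESBL |
| no | yes | yes | **none** | carbapenemase |
| no | yes | no | **none** | carbapenemase |
| no | no | yes | none | none |
| no | no | no | none | none |

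Six combinations carry at least one of the enzymes, and three of those six get no Table 3 class. These are the carbapenem-susceptible ESBL producer and both forms of the carbapenemase-only isolate. These are counts of combinations, not of isolates.

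**Step 2. What follows without any outside figure.** Every carbapenemase-only isolate is left out (100% of that group). Every carbapenem-susceptible ESBL producer without a carbapenemase is left out as well.

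**Step 3. What cannot be sized.** Let s be the share of ESBL-positive, carbapenemase-negative isolates that are carbapenem-resistant. The share of that group left out is 1 − s. The documents give no value for s, so the values below are assumptions that show only how far the answer moves:

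| Assumed s | Left out, 1 − s |
|---|---|
| 1% | 99% |
| 5% | 95% |
| 10% | 90% |
| 25% | 75% |
| 50% | 50% |
| 75% | 25% |

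The documents also give no frequency for carbapenemase-only isolates, so the shortfall in that indicator cannot be sized either.

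**Step 4. Which results use these labels.** Of the seven microbiological indicators in Table 2, three do: ESBL *E. coli*, ESBL *K. pneumoniae* and carbapenemase-producing *Enterobacteriaceae*. The remaining 7 − 3 = 4 do not (MRSA, MDR *P. aeruginosa*, MDR *A. baumannii*, *C. difficile*). The matching carrier-screening and wastewater phenotypic classes use them. The wastewater molecular panel (section 2.7.2) and the correlations of antimicrobial concentration with consumption (section 2.9) do not.

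**The case against.** The strongest reply is that the two rows were never meant as full definitions. Both are conditionals that settle an overlap: an isolate with both enzymes goes to carbapenemase, and a carbapenem-resistant isolate with ESBL but no carbapenemase stays with ESBL. Several features support this reading:

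- MRSA is a counted indicator and has no row, so Table 3 is not a complete list.
- Section 2.7.1 has resistance mechanisms determined by EUCAST criteria before the table is introduced.
- Samples are plated on a combined ESBL/CRE medium. Recovering ESBL separately would make little sense if only carbapenem-resistant isolates could count.

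This reading is plausible and probably reflects the intent. It does not remove the point. The text calls the rows definitions, says they will be applied, and prints no base definitions for them to supplement. On this reading too, the table needs correcting.

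The reply also has force on consequences. No section says that centers' counts pass through Table 3. Section 2.5 has data taken from existing records including those of microbiology units, and section 2.4 has participants enter the numerators. A laboratory that has found ESBL may simply report ESBL. The documents therefore show a faulty rule, but not that counts have already been distorted by it.

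**Conclusion.** The contradiction between Table 3 and Table 2 stands on the printed text, and Table 3 is wrong as written. If it is applied literally, three of the seven microbiological indicators and the matching carrier and wastewater phenotypic classes are undercounted by an unknown amount.

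A reader might go further in two ways, and the documents support neither:

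- **That most ESBL isolates, perhaps 90% or more, would be lost.** More than half are lost only if s is below 50%, and a loss of at least 90% needs s of 10% or less. The documents give no value for s.
- **That no resistance effect or wastewater correlation could be read.** Four microbiological indicators, the molecular wastewater results and the concentration–consumption correlations do not depend on these rows.

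The main variable, total antimicrobial consumption (section 2.3.2), its interrupted time series and the sample size are untouched. The conclusion rests on one assumption: that Table 3 is used as the operative rule, as section 2.7.1 says.

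**What to change.** Rewrite the two rows so that every isolate carrying either enzyme has exactly one class, in line with Table 2:

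- Carbapenemase-producing: any carbapenemase detected, with or without ESBL.
- ESBL-producing: ESBL detected and no carbapenemase, whatever the carbapenem susceptibility.

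Add a note to Table 2 that an isolate with both enzymes counts once, under carbapenemase.

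Then confirm with each center's laboratory and the coordinating laboratory which rule was used in the pre-intervention and intervention phases, and record the answer. Where isolate-level results with enzyme status are available, reclassify the earlier counts. Where only monthly totals exist, report the rule behind them and any change between phases.

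The text change is two table rows and a note. The query to laboratories is modest work. The cost of reclassification cannot be judged from the documents, which describe monthly numerators and do not say whether isolate-level results are kept. Because the intervention phase is under way, the query is best made now.
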